#### Intervention

The intervention that will be presented and evaluated in this trial will be a training package for the enrichment of couples’ sexual interactions, which will enhance the sexual satisfaction of couples (Table 1). This intervention will be compared with the usual care provided at the urban health centers.

**Table 1 Tab1:** Headings and Learning objectives of the enrichment of couples’ sexual interactions training package

Heading	Learning objective
The importance of skills teaching in marital relationships	Understanding the importance of sex education in the formation of appropriate sexual life Understanding the importance of proper sexual interactions in marital life
Effective communication of couples	Knowing the concept of communication Understanding the growing steps of marriage Understanding the effective communication factors with the spouse Recognizing effective cases in the strength or destruction of communications Earn the ability to talk to spouse about sex
Establish effective communication	The Impact of communication on effective Interpersonal Interactions Communicating to express feelings and ideas, Individual responsibility Good listener features Effective communication skills practice The influence of culture in communication patterns
Anatomy and function of sexual and reproductive organs	Knowing of sexually-reproductive organs of men and women Familiarity with the performance of sexually-reproductive organs of men and women Understanding male and female sexual responses
Vocabulary and sexual response patterns	Understanding sexual vocabulary Understanding the stages of sexual intercourse between husband and wife comprehending the cycle of sexual behaviors in men and women
Skills in sexual relationships	Familiar with the factors affecting good sexual interactions perceiving the basics of sexual life Determine the sexual lifestyle of couples by themselves Understanding the stages of sexual relationship Talking with spouse about the priorities of sexual life, tendencies, fantasies, types of touches.
Sexual health	Understanding the Importance of Sexual Diseases Understanding the factors that cause sexually transmitted diseases Understanding transferring ways of sexually transmitted diseases Familiarity with the symptoms of sexually transmitted diseases Identifying ways to prevent sexually transmitted diseases
Sexual relationships during pregnancy	Recognizing communication problems during pregnancy Understanding physiology of pregnancy Familiarity with how to have sex during pregnancy Learn important tips on sexual relationships in different months of pregnancy Familiarity with different modes of doing sex during pregnancy Recognition of sexual behaviors in the postpartum period
Sexual problems	Identifying common causes of sexual problems Understanding couples from their sexual life inhibitors Identifying couples’ sexual problems by themselves Understanding sexual dysfunctions in men and women Recognizing the effective factors in creating sexual disorders in men and women Action to treat sexual dysfunction

#### Description of intervention

The training package of enrichment of couples’ sexual interactions were designed based on the content of individual interviews with 22 couples in the qualitative phase and the results of the cross-sectional phase of study (*n* = 400) and according to the IMB model. This package includes the 18-h Marital and Sexual Skills Training Workshop, the presentation of the “My Soul Partner” book which is given to each couple for free and sending short messages.

The “My Soul Partner” book is written by second author who is **sexo**logist. The aim of this book is skill training of intimate and sexual relationships of couples in the form of religious and cultural values and norms of the Iranian community that empower couples to have a healthy and intimate marital life. The book forms the educational content of the workshop, which includes the topics of the effective communications of spouses, the anatomy and performance of reproductive organs, the vocabulary and patterns of human sexual response, the sexual communication skills, sexual relationships during pregnancy, sexual health and sexual problems. The content will be presented using collaborative approaches such as, the group discussion, role playing and question and answer in the workshop, and the couples will solve the exercises and self-tests in the book and discuss the results. The 18-h workshop will be planned in the form of six 3-h workshop in 6 consecutive weeks that will be considered rest and catering among meeting sessions for participants. The location of workshops will be at one of the health centers in the center of the city. It is convenient to move all participants from different parts of the city at this central location. The time of holding the workshop will be determined by the participants and will be tried in a way that does not interfere with the working hours of the participants. Teaching in workshops will be handled by two people from the research team.

#### Description of the control

Couples in control group will not receive an intervention after completing the baseline questionnaire, and receive only the reproductive health care provided at the urban health centers. The services provided by the family and community health unit in urban health centers for couples include family planning, counseling and treatment for STDs and HIV/AIDS, premarital training, counseling and screening for reproductive system cancers including breast and cervical cancer. But there is no service in the field of sexual health. Couples in two groups receive routine services.

### Outcome measures

#### Primary outcomes

The primary outcomes of study include the facts that couples will learn about the correct sexual interactions, the identification of the right and wrong sexual beliefs, the attitude towards sexual relations, understanding subjective and social norms in the field of sexual health promotion behaviors, objective skills for the correct sexual behavior and self-efficacy in using these skills in sexual life situations and couples sexual behaviors. Mean score of couples’ sexual information, motivation and behavioral skills will be assessed 4 months after the end of intervention.

#### Secondary outcomes

Mean score of couples’ sexual satisfaction at 4 months after the end of the intervention.

#### Outcome assessment

The outcomes will be measured through the online individual, close ended questionnaire, which is designed on Google Form (https://docs.google.com/forms) and its link will be sent to mobile phone’ participants via accessible social networks (Telegram, WhatsApp messenger, Instagram, IMO and LinkedIn). Given the confidentiality of the questions, this method has been chosen to enhance the privacy of participants and feel more comfortable in answering the questions. Only the main investigator will be able to view the responses. The questionnaires will be administered at the baseline (before assigning couples to the study arms) and 4 months after the end of the intervention. To evaluate the primary outcomes, the SIMBS questionnaire will be used which was designed by the research team based on individual interviews with couples and according to the IMB model and its psychometric properties were confirmed in 200 couples (*n* = 400). To evaluate the secondary outcome, Larson’s Sexual Satisfaction Questionnaire [24] will be used, whose validity and reliability has been confirmed in Iranian couples [8]. The main investigator will contact the couples at the baseline and four months after the intervention and explain how they will fill the questionnaire. This description will be sent in writing along with the questionnaire and instructions for completing the questionnaire. Also, a phone number will be given to couple to contact the research team if they have any questions. Then the questionnaire link will be sent to them. All participants will send their responses via mobile phone. The proper security measures will be taken to assured and arcane transfer data to a secure database.

### Duration of the study

The duration of the intervention from entry to study until the evaluation of the consequences will be 6 months.

### Follow up and data collection

After the workshops, the couples will be followed for 4 months. During this time, they will be asked to read the “My Soul Partner” book carefully with their spouse and complete the exercises and talk about the results together. Also short messages in the field of skill training for sexual relationship will be sent to them by cell phone. Short messages will be based on the content of the book and workshops, which will be sent to recall and review the submitted content. These messages will be transmitted through the creation of a telegram group, which all couples in the intervention group will be members of, and sent as a message every week. Couples will also be able to ask questions about the content of the book and workshops, from the administrators of the group who will be a member of the research team and will provide an answer within 48 h. Data will be collected at the baseline and at four months after the intervention. The original researcher will contact the participants at baseline and at 4 month after the intervention and will coordinate with them to send the questionnaire link. Participants will be asked to respond and submit their responses within a week. If they do not reply within a week, they will be contacted three times. In case of non-response after three times, they will be excluded from the study.

### Database

Participants’ responses to the questionnaire will be visible only to the primary researcher after being submitted online. This data will be saved securely on a server with a strong back up system.

### Sample size

According to the results of studies conducted in Iran about the effect of sexual health education on sexual satisfaction of couples [14], the maximum significant difference was found in sexual satisfaction score between intervention and control groups was 5.38. A sufficient sample size to detect the maximum difference between the intervention and control groups in the sexual satisfaction score with 80% of the power at significant level α = 0, 05 and considering the rate of loss 5% will be 200 people. Thus, 50 couples (*n* = 100) will be assigned to the intervention group and 50 couples (n = 100) will be assigned to the control group.

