#### Randomization

In this study, a simple randomization method will be used. The unit of randomization will be a couple. Firstly, eligible couples will be assigned randomly to either the intervention or the control group according to the Random Number Table, and then the randomization will continue until the balance is established in terms of the size of the groups. In order to ensure allocation concealment, the central randomization method will be used so that a random sequence was given to the original researcher at one of the centers and the samplings of couples in other centers are done simultaneously. Other colleagues at other centers will contact the researcher through the telephone and ask questions about the random allocation of the couple to the special group.

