### Statistical analysis

First the data will be tested for normality, outliers and missing data. Descriptive statistical analysis of the demographic characteristics of two groups will be done to ensure comparability of data in intervention and control groups. To compare the primary (mean score of couples’ sexual information, motivation, behavioral skills and behavior) and secondary (mean score of couples’ sexual satisfaction) outcomes of the study, before and 4 months after the intervention in each group, the paired t-test will be used. Also, independent t test and Analysis of Covariance (ANCOVA) will be performed to compare the outcomes before intervention in two groups and after intervention in two groups. In order to determine the score of sexual satisfaction of couples (female and male score), the principal component analysis will be used and the male and female scores will be converted to one score.

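### The sample size is set in persons with no SD and no allowance for spouse correlation although couples are randomised, and the unit of analysis for the primary SIMBS outcomes is not fixed

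*Protocol article*

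**What the plan says.** The Randomization section of the protocol article states: "The unit of randomization will be a couple". Under Outcome assessment, each spouse fills in a separate online questionnaire.

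The Sample size section takes its effect from earlier Iranian work, in which "the maximum significant difference was found in sexual satisfaction score between intervention and control groups was 5.38". It asks for a sample "with 80% of the power at significant level α = 0, 05", and concludes that the number, "considering the rate of loss 5% will be 200 people". The persons are then paired: 50 couples go to the intervention, and "50 couples (n = 100) will be assigned to the control group". No SD, spouse correlation or design effect is given.

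Under Statistical analysis, "independent t test and Analysis of Covariance (ANCOVA) will be performed to compare the outcomes before intervention in two groups", and likewise after it. No couple term appears. One rule turns two spouses into one observation: male and female sexual satisfaction scores are combined by principal component analysis. No such rule is given for the primary outcomes (information, motivation and behavioral skills, measured by SIMBS).

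**The concern.** Spouses share their allocation and rate the same relationship. In the intervention arm they also attend the same workshops and are asked to work through the book together. Their scores can be expected to correlate positively, so two spouses carry less information than two unrelated people. This matters in two places.

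- **Power for sexual satisfaction.** The sizing counts 100 persons per arm, but the analysis has at most 50 couple scores per arm. The variance of a couple score still contains the spouse correlation, so merging spouses does not bring back the power of 100 independent persons.
- **Type I error for the primary outcomes.** If SIMBS scores are compared person by person with an ordinary t test, the standard error is too small and a positive primary result can be false more often than 5% of the time. The Discussion says that effective results will be presented to policy makers for national implementation.

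**Working it through.** **Inputs from the protocol article.** Difference 5.38; power 80%; alpha 0.05; loss 5%; 200 persons, that is 100 persons or 50 couples per arm; 1:1 allocation.

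**Assumptions, because the article gives no value.** Two-sided test; equal SD and equal effect in husbands and wives; spouse correlation ρ of 0.1, 0.3 or 0.5; for ANCOVA, a correlation of 0.5 between the baseline and follow-up couple scores. Normal approximation throughout.

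**Step 1: the plan's own figure.** Without an SD, 200 cannot be reproduced, only back-solved. After 5% loss, 100 × 0.95 = 95 persons per arm. For independent persons:

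- standardised difference = (1.960 + 0.842) × √(2/95) = 0.406
- implied SD = 5.38 / 0.406 = 13.2 (13.24 unrounded)

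So 200 fits an independent-persons calculation at that SD. This does not show that the authors used it: some SD can be found for any sample size.

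**Step 2: power with couples.** The mean of two spouses has variance SD²(1+ρ)/2. With 47.5 couples per arm, the standard error of the difference is SD × √((1+ρ)/47.5). Power = Φ(0.406/√((1+ρ)/47.5) − 1.960). At ρ = 0.3 this is Φ(2.457 − 1.960) = 69%.

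The first principal component of two positively correlated standardised scores weights them equally, so the planned couple score carries the same factor 1+ρ.

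**Step 3: couple-level ANCOVA.** Residual variance is multiplied by 1 − 0.5² = 0.75. At ρ = 0.3, power = Φ(2.457/√0.75 − 1.960) = 81%.

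**Step 4: largest SD that still gives 80% unadjusted.** 13.24/√(1+ρ).

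**Step 5: type I error of a t test on individuals.** The test uses a variance too small by the factor 1+ρ, so the true error is 2(1 − Φ(1.960/√(1+ρ))).

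| ρ (assumed) | Power, unadjusted, SD 13.24 | Power, couple ANCOVA | Largest SD for 80% | Couples per arm for 80% unadjusted, with 5% loss | Type I error, t test on individuals |
|---|---|---|---|---|---|
| 0.1 | 76% | 87% | 12.6 | 56 | 6.2% |
| 0.3 | 69% | 81% | 11.6 | 66 | 8.6% |
| 0.5 | 63% | 75% | 10.8 | 76 | 11.0% |

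Using the t distribution in place of the normal gives 62% in the last row of the unadjusted column.

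**Step 6: simulation check (40,000 trials).** With 50 couples per arm, the person-level t test rejected a true null in 8.9% (ρ = 0.3) and 11.1% (ρ = 0.5) of trials. The couple-level test stayed at 4.9% to 5.2%. With 47 couples per arm, the couple-level test had 68% and 61% power.

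**The case against.** Two stronger readings are tempting, and the article supports neither.

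A reader might infer that all the tests treat 200 people as independent. That is not so. Sexual satisfaction is reduced to one score per couple, so its between-group test has the randomised unit as its unit and keeps its 5% error as far as spouse correlation is concerned. For the SIMBS outcomes the unit is simply not stated. The article describes them as mean scores of the couples, which could mean a couple average. The person-level reading is likelier, because the same description is used for satisfaction and a merging step is still added for that outcome alone. But it remains a reading, and the error rates depend on it.

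A reader might also infer that 80% power is not delivered. That is not shown. The article calls 200 sufficient, not the minimum. With an SD of 10, independent persons would need 116 people including loss, and even at a spouse correlation of 0.5 this becomes 116 × 1.5 = 174, below 200. The plan also names ANCOVA, which on the assumptions above reaches 81% at a correlation of 0.3, though only 75% at 0.5.

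It may be said that a condensed article leaves the model for couples to a fuller document. That has some force for model detail. It does not cover a stated sample size and power whose basis in persons does not match the randomised unit, or named tests that lack a couple-level score for the primary outcomes.

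Sharing of workshop groups in the intervention arm is a further possible source of correlation. The number of groups is not stated, so it is secondary here.

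**Conclusion.** The point holds in a conditional form. The sizing in persons does not match couple randomisation or the one-score-per-couple analysis of its own outcome, and the power statement cannot be verified without an SD and a spouse correlation.

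- **Power.** If 200 is the exact independent-persons figure (two-sided 5%, 5% loss), any positive spouse correlation puts an unadjusted comparison below 80%: by about 4, 11 and 17 percentage points at assumed correlations of 0.1, 0.3 and 0.5. Baseline adjustment or a smaller true SD may offset this.
- **Type I error.** If the primary SIMBS outcomes are tested on individuals with the named t test, a nominal 5% becomes roughly 6% to 11% over the same range. For a person-level ANCOVA the inflation would depend on the spouse correlation that remains after baseline adjustment, which was not calculated.

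The omission is certain. The size of its effect rests on assumed values. It should be corrected before analysis, because the natural reading of the plan gives standard errors that are too small on the primary outcomes.

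**What to change.** 1. Make the couple the unit for every outcome. Either fit a linear mixed model to individual scores with a random couple effect, arm, spouse sex and baseline score, or use ANCOVA on a couple score defined for each SIMBS outcome as well as for satisfaction.
2. State the SD and the spouse correlation. For SIMBS, both can come from the team's own validation sample of 200 couples (Study overview). For satisfaction, give the source of the SD behind the 5.38-point difference, and a spouse correlation or a range for it.
3. Keep 100 couples and restate the power in couples, with design effect 1+ICC and any baseline adjustment relied on, in place of the statement that 200 people give 80% power.
4. If there are several workshop groups, say so and consider a workshop-group effect in the intervention arm.

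The cost is rewording of the Sample size and Statistical analysis sections, with no extra couples. The restated power may be less favourable. If the sponsor wants 80% from an unadjusted comparison at the implied SD, 50 couples per arm are too few at any of the correlations tabulated above, and the choice between baseline adjustment, lower stated power and more couples should be made openly.

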### Statistical analysis

First the data will be tested for normality, outliers and missing data. Descriptive statistical analysis of the demographic characteristics of two groups will be done to ensure comparability of data in intervention and control groups. To compare the primary (mean score of couples’ sexual information, motivation, behavioral skills and behavior) and secondary (mean score of couples’ sexual satisfaction) outcomes of the study, before and 4 months after the intervention in each group, the paired t-test will be used. Also, independent t test and Analysis of Covariance (ANCOVA) will be performed to compare the outcomes before intervention in two groups and after intervention in two groups. In order to determine the score of sexual satisfaction of couples (female and male score), the principal component analysis will be used and the male and female scores will be converted to one score.

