### Objectives and hypothesis

The aim of this randomized controlled trial is to compare the efficacy of sexual and marital skills training package using information, motivation and behavioral skills model on sexual satisfaction of new couples in Iran to routine sexual care program that provided at governmental health centers. It is hypothesized that sexual and marital skills training package will increase sexual information, sexual motivation and sexual behavioral skills of participating couples which will improve sexual satisfaction and ultimately their sexual health compared to control group couples.

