### Trial design

This trial is designed as a randomized, controlled, superiority trial with two parallel groups. Randomization will be performed with a 1:1 allocation.

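### The analysis section lists within-arm, baseline and two between-arm tests without making one baseline-adjusted comparison at 4 months decisive

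*Protocol article*

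**What the plan says.** The Statistical analysis section of the protocol article names three procedures for the outcomes.

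- Within each arm, for the primary and the secondary outcomes: "before and 4 months after the intervention in each group, the paired t-test will be used".
- Between arms: "independent t test and Analysis of Covariance (ANCOVA) will be performed to compare the outcomes before intervention in two groups". The sentence goes on to add the comparison of the two groups after the intervention.
- No test is identified as the one that decides superiority, and the ANCOVA covariate is not named.

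The rest of the article frames a between-arm question:

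- Trial design: "This trial is designed as a randomized, controlled, superiority trial with two parallel groups", with 1:1 allocation.
- Objectives and hypothesis: the package is expected to raise information, motivation and skills, "which will improve sexual satisfaction and ultimately their sexual health compared to control group couples".
- Sample size: the quantity powered for is a difference between arms, "the maximum significant difference was found in sexual satisfaction score between intervention and control groups was 5.38".
- Outcome assessment: "The questionnaires will be administered at the baseline (before assigning couples to the study arms) and 4 months after the end of the intervention". A baseline score taken before allocation is therefore available for adjustment.

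**The concern.** A before-after test inside one arm makes no use of the control group. It mixes any effect of the package with retest effects, regression to the mean and ordinary change over time. Both arms answer the same self-report questionnaires twice, so such shared change is possible. A significant result in the intervention arm beside a non-significant one in the control arm is not evidence that the arms differ.

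The between-arm question then appears to receive two tests at 4 months with no ranking. If both are run and the smaller p-value is reported, the error rate is no longer the nominal 5%. Testing baseline scores between randomised arms examines a null hypothesis that allocation has already made true.

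The Discussion says that, if the trial shows an effect, the results will go to policy makers for national use. The basis for that claim should be the randomised contrast, and a reader should be able to tell in advance which analysis supplies it.

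**Working it through.** **The plan's own figure.** The article gives no error rate for this set of tests. The nearest figure is the sample size of 200 people for a difference of 5.38, 80% power, alpha 0.05 and 5% loss. It cannot be reproduced because no SD is stated. Working backwards, with a two-sided test and persons counted as independent, n per arm = 2(1.96 + 0.84)² / d². Setting n = 100 × 0.95 = 95 gives d of about 0.41, so an SD of about 5.38/0.406 = 13.2. This is used here only to confirm that the powered contrast is between arms.

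**Count of tests per outcome.** On the literal wording there are 2 paired tests (one per arm) plus 2 between-arm tests at each of 2 times, so 2 + 2 × 2 = 6. If the t-test is meant for baseline and the ANCOVA for follow-up, the count is 2 + 1 + 1 = 4.

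**Simulation inputs.** From the article: 50 couples per arm and 5% loss, so 50 × 0.95 = 47.5, taken as 47 couple scores per arm. Assumed, because the article gives neither: a baseline to follow-up correlation r of 0.3, 0.5 or 0.7, and a change common to both arms of 0, 0.2, 0.3 or 0.4 SD. There is no true difference between arms. Each setting has 20,000 runs, so the Monte Carlo standard error near 5% is √(0.05 × 0.95 / 20,000) = 0.15 percentage points.

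**Step 1: two competing between-arm tests at 4 months.** Type I error, as the range over the four common changes:

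| r (assumed) | t-test alone | ANCOVA alone | better of the two |
|---|---|---|---|
| 0.3 | 5.0–5.2% | 4.8–5.2% | 6.2–6.6% |
| 0.5 | 4.9–5.1% | 4.6–5.2% | 7.0–7.4% |
| 0.7 | 4.9–5.2% | 4.7–5.2% | 8.0–8.5% |

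Either test alone holds its level. Choosing between them after seeing the results gives about 6% to 9%.

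**Step 2: the pattern of intervention arm significant, control arm not.** If both arms truly change by the same amount and each paired test has power p, the pattern has probability p(1 − p). With no change, p = 0.05 and this is 0.05 × 0.95 = 4.75%. At r = 0.5 and a change of 0.3 SD, the simulated p is 0.525 and 0.525 × 0.475 = 24.9%, against 25.4% simulated directly. All settings:

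| Common change (assumed) | r = 0.3 | r = 0.5 | r = 0.7 |
|---|---|---|---|
| 0 | 4.8% | 4.6% | 4.7% |
| 0.2 SD | 16.1% | 20.0% | 24.0% |
| 0.3 SD | 23.6% | 25.4% | 19.3% |
| 0.4 SD | 23.4% | 18.1% | 6.1% |

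The rate falls again at larger changes because both arms then become significant.

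**Step 3: what ANCOVA offers.** Its variance relative to the unadjusted t-test is 1 − r², which is 0.91, 0.75 and 0.51 at r = 0.3, 0.5 and 0.7. At d of about 0.41 this means 87, 72 and 49 independent units per arm, against 95 unadjusted.

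**The case against.** A reader might infer that the trial will judge superiority by the paired tests. The text does not say so. It gives those tests the task of describing change within each group and gives the comparison of groups to other tests. Being listed first does not make a test decisive. This part of the objection stands, and it limits the 16% to 25% figure: that rate arises only if both arms share a true change of about 0.2 to 0.3 SD and someone treats the pattern as inference, which the plan does not propose.

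A reader might also infer that the plan forgoes baseline adjustment and its precision. It does not plainly do so, because ANCOVA is listed and baseline scores are collected. The saving in Step 3 would be lost only if the t-test were used in its place.

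The between-arm sentence can also be read as pairing the t-test with baseline and the ANCOVA with follow-up. That reading is sensible, since a baseline-adjusted ANCOVA of the baseline score itself would be meaningless. Only one between-arm test then exists at 4 months and the 6% to 9% does not arise. The sentence does not say this, however. Even if it did, the unranked paired tests and the baseline significance tests would remain.

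Finally, detail about the primary model can be left to a fuller protocol or SAP. That is fair for omissions. Here the article commits to a list of tests, and the point concerns that commitment.

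**Conclusion.** The point holds as a modest fault in the stated methods. The paired tests do not answer the superiority hypothesis, the baseline tests carry no information after randomisation, and nothing in the text marks the baseline-adjusted 4-month comparison as decisive. On the literal wording, picking the better of two between-arm tests gives a type I error of about 6% to 9%. That rests on assumed correlations of 0.3 to 0.7 and 47 couple scores per arm. One prespecified ANCOVA stays at 4.6% to 5.2% whatever the common change. The within-arm pattern is a risk of interpretation: about 5% of null trials with no common change, and 16% to 25% with an assumed common change of 0.2 to 0.3 SD. The documents do not support a claim that effects will be judged within arms. The missing SD and the correlation between partners are separate matters and do not bear on this conclusion.

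**What to change.** In the Statistical analysis section, state that superiority on each outcome is judged only by the between-arm difference at 4 months, estimated by an ANCOVA of the follow-up score with the baseline score as covariate and reported with its 95% CI. Remove the post-intervention independent t-test and the significance tests of baseline scores. Report within-arm changes as means and SDs, without p-values.

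This is a free improvement. The baseline questionnaire is already planned before allocation, so no data collection, sample size or visit changes; only the wording does.
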